# Preparatory Research

We have established a sleep and cancer research programme focusing on the aetiology, impact, and non-pharmacological management of insomnia in breast cancer patients. Our research programme has enabled the development of an international breast cancer research register (n=879) and PPI network. Informed by this network, our next step is to evaluate whether we can prevent the development of ID in this at-risk population by offering an early, evidence-based insomnia intervention that targets acute sleep disturbance. Treating acute insomnia has been identified as a priority issue by a task force of experts from the World Sleep Society in their recent guideline for the diagnosis and treatment of insomnia ([13](#_ENREF_13)). Our preparatory pilot work, comprising systematic literature reviews, qualitative studies, observational analyses, RCTs and public engagement work, all validate the proposed study. We recently demonstrated that exhibiting acute sleep disturbance in response to breast cancer diagnosis results in a six-fold increase in insomnia prevalence ([8](#_ENREF_8)) and is a risk factor for the development of ID ([11](#_ENREF_11)). We have also demonstrated that ID is deleterious for psychological and physical wellbeing in breast cancer patients ([10](#_ENREF_10), [14](#_ENREF_14)). Our qualitative studies ([9](#_ENREF_9), [10](#_ENREF_10)) reveal that breast cancer patients implement sleep extension behaviours, intended to compensate for sleep loss, that increase their risk of ID. SRT is an established treatment for ID that works by addressing these sleep extension behaviours to stabilise the sleep-wake schedule. A recent meta-analysis of RCTs by our team demonstrates that SRT significantly improves insomnia severity and sleep continuity in patients with ID ([12](#_ENREF_12)). Therefore, it offers promise as an early therapeutic approach for acute insomnia. Our data also show that insomnia interventions (such as SRT) improve concomitant symptoms like anxiety, depression, and fatigue in breast cancer patients ([14](#_ENREF_14), [15](#_ENREF_15)). In addition, because SRT leads to reduced sleep variability and improved sleep consolidation and quality, it may minimise these other prevalent cancer-related side effects as they emerge, so sleep is a promising transdiagnostic therapeutic target for wellbeing more generally. However, no research has evaluated SRT for acute insomnia in cancer patients, so it is unclear whether it is tolerable and efficacious for patients undergoing cancer treatment.

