6. *Consensus Sleep Diary:* Prospective daily diary entries will be used to assess self-reported sleep patterns over a 7-day period. Sleep diaries are a reliable and valid index of insomnia and have been used as an outcome measure in efficacy studies on insomnia. During the baseline, intervention, 6 week and 12 week assessment, prospective self-report data will be collected using the consensus sleep diary. This consists of an assessment of bedtime, sleep onset latency, wake time after sleep onset, rise time, total sleep time, ratings of sleep quality and napping behaviour.
7. *Actigraphy:* The actigraphy device is a wristwatch like device that measures activity through an accelerometer (motion sensor that records the occurrence and degree of motion). Reduced activity can be used as a proxy for sleep, thus providing information about the sleep-wake cycle.
8. *The Client Service Receipt Inventory (CSRI):* The CSRI is a research tool that collects information on service utilisation, income, accommodation and other cost-related variables.
9. *Patient Satisfaction with Treatment:* An adapted version of the Patient Satisfaction Questionnaire Short Form (PSQSF) will be used to assess patient’s treatment satisfaction with the intervention.
10. *Safety:* Adverse events unrelated and related to the interventions will be recorded during treatment. A side-effects inventory, which was developed for individuals with insomnia undergoing behavioural treatments, will be used. Serious adverse events such as deaths, suicide attempts, and serious accidents will also be recorded. We will also encourage patients to contact us with any changes to their health and wellbeing.

Table 2: Overview of scheduled study assessments

| **Measures** | **Screening** | **Baseline (T0)** | **During SRT** | **6 weeks post-randomisation** | **12 weeks post-randomisation** |
| --- | --- | --- | --- | --- | --- |
| ISI, PHQ-9, GAD-7, FACT-F, |  | X |  | X | X |
| Sleep diary |  | 7 days | Daily | 7 days | 7 days |
| Actigraphy |  | 7 days |  | 7 days | 7 days |
| Enrolment logs (recruitment) | X |  |  |  |  |
| Fidelity rating scale (therapist adherence) |  |  |  | X |  |
| Intervention attendance logs (patient engagement) |  |  | X |  |  |
| Client Service Receipt Inventory (control group contamination) |  |  |  | X | X |
| Adverse Events |  |  | X | X | X |
| Treatment Satisfaction |  |  |  | X |  |
| Exit interviews (intervention acceptability) |  |  |  | X |  |

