# Adverse Event Ascertainment and Reporting

12.1 Definitions of Adverse Events, Serious Adverse Events, and Unanticipated Problems

Adverse events (AEs) will be defined as any unwanted medical event, reaction or side effect that occurs during the research study. Any relationship to study procedures will be determined and each AE defined as either unrelated or possibly, probably, or definitely related to participation in the study. The severity of the AEs will be determined by the type and outcome of the AE. Serious AEs (SAEs) are classified as such if the event results in death, disability, hospitalisation, deformation, congenital abnormality birth defects or any medical events that might lead to the outcomes listed above. The classification of the AE is determined irrespective of the relationship to the study interventions. An adverse event will be classified as an unanticipated problem (UP), if the AE is unexpected, if it is related or possibly related to the study procedures, and if the occurrence indicates that the participants or others are placed at greater risk by completing the study that previously assumed.

12.2 Unsolicited/Solicited Assessment and Reporting of Adverse Events and Unanticipated Problems:

AEs will be assessed systematically using a side effects inventory. Patients will also be encouraged to disclose any AEs, new symptoms or major life events during each assessment (unprompted side effects assessment). Additionally, sleep diaries and self-report questionnaires will be reviewed for any emerging symptoms. All AEs will be recorded in an adverse event reporting form, where a detailed description of the event and follow-up action will be recorded. Additionally, the form will provide an opportunity to record whether the event is classified as serious, whether it is related to the study procedures, and whether it is an unexpected AE (see definitions above). The adverse event form will be passed to the CI for review. All SAEs will be reported to the Ethics Committee within 48hrs and UPs that do not meet criteria for SAEs will be reported to the CI within 48hrs, who is responsible to reporting to the Ethics Committee within 30 days. All remaining AEs will be collated for the steering group committee.

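### The side-effects inventory has no scheduled pre-treatment reading, so its symptoms cannot be classed as new or worse for an individual patient

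*Protocol*

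**What the plan says.** Item 10 of the Assessment Tools (Procedures) says: "Adverse events unrelated and related to the interventions will be recorded during treatment". It then names the instrument: "A side-effects inventory, which was developed for individuals with insomnia undergoing behavioural treatments, will be used".

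The row in Table 2 reads "Adverse Events | | | X | X | X". The columns are, in order, Screening, Baseline (T0), During SRT, 6 weeks and 12 weeks, so the first two are empty.

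Section 12.2 gives the inventory its role: "AEs will be assessed systematically using a side effects inventory". Two further sources are listed there: "Patients will also be encouraged to disclose any AEs, new symptoms or major life events during each assessment (unprompted side effects assessment"), and "sleep diaries and self-report questionnaires will be reviewed for any emerging symptoms".

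Section 12.1 defines an adverse event as "any unwanted medical event, reaction or side effect that occurs during the research study". It requires each event to be graded as unrelated to study participation or as possibly, probably or definitely related. It gives no rule on onset or worsening from baseline.

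**The concern.** Eligibility (Participants, inclusion criteria) requires poor sleep with accompanying night-time or daytime symptoms in someone newly diagnosed with breast cancer. The unwanted effects to be expected from SRT resemble that starting state. The protocol itself describes sleep deprivation as a common side effect of SRT (Participants), and plans advice on daytime sleepiness in session 1 (Interventions). Some inventory symptoms are therefore likely to be present before treatment.

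Without a T0 reading on the same form, a positive item at 6 weeks may be old, new or worsened, and the form cannot show which. The relatedness grade then rests on recall and judgement, in a trial where patients and therapist know the allocation (Study Design).

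What is at stake is the tolerability information. The Background gives the tolerability of SRT in these patients as a question needing research. An analysis plan written later cannot recover a baseline reading that was never taken.

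**Working it through.** **1. Is the inventory scheduled before treatment anywhere?** Four places could do so.
- Table 2: Screening and Baseline are blank for adverse events.
- Item 10: recording is during treatment.
- Study Assessment Points: the baseline battery covers sleep, fatigue and mental health, plus diary and actigraphy. Side effects are not mentioned.
- Section 12.2: the inventory is the systematic tool, with no timing and no comparison with an earlier score.

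None schedules it.

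**2. Do the references to new and emerging symptoms fill the gap?** In section 12.2 the first belongs to unprompted disclosure and the second to the review of diaries and questionnaires. Neither is attached to the inventory.

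**3. How much could pre-existing symptoms matter?** The protocol gives no symptom rates and no figure of its own to reproduce here, so this is an illustration on assumed values. Let b be the share of both arms with a symptom before treatment, all persisting. Let i be the share of those without it in whom SRT newly causes it, and let SHE cause none. Then:
- SRT prevalence p = b + i(1 − b)
- pre-existing share of SRT reports = b / p
- SRT minus SHE difference = p − b
- 95% CI half-width = 1.96 × √[p(1 − p)/20 + b(1 − b)/20], with 20 per arm from Data Analysis

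| b | i | p | Pre-existing share | Difference (points) | 95% CI half-width (points) | Power |
|---|---|---|---|---|---|---|
| 0.2 | 0.2 | 0.36 | 56% | 16 | 27 | 20% |
| 0.2 | 0.4 | 0.52 | 38% | 32 | 28 | 56% |
| 0.4 | 0.2 | 0.52 | 77% | 12 | 31 | 11% |
| 0.4 | 0.4 | 0.64 | 62% | 24 | 30 | 32% |
| 0.6 | 0.2 | 0.68 | 88% | 8 | 30 | 8% |
| 0.6 | 0.4 | 0.76 | 79% | 16 | 28 | 19% |

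First row: p = 0.2 + 0.2 × 0.8 = 0.36, and 0.2/0.36 = 56%.

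**4. Dilution of the contrast.** Take b = 0.5, with new symptoms in 20% (SRT) and 5% (SHE) of those without them. Raw prevalence is 0.5 + 0.2 × 0.5 = 60% against 0.5 + 0.05 × 0.5 = 52.5%, a gap of 7.5 points. Among patients free of the symptom at T0 it is 20% against 5%, a gap of 15 points. With 20 per arm, about 12 SRT patients report the symptom, and 10 of them had it before.

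**5. What does the control arm cover?** The 6- and 12-week columns carry no arm restriction, so SHE supplies a background rate there. The only earlier column is During SRT, so nothing is scheduled for SHE patients over the matching 4-week period.

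**The case against.** The opposing case is substantial, and most of it limits how far the point goes.

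- *Counting.* A reader might infer that every pre-existing symptom will be counted as an adverse event. No section says that each positive inventory item becomes one or that raw counts will be reported. Events are graded for relatedness, and tabulation rules may sit in an analysis plan that is not to hand.
- *Identifiability.* A reader might also infer that treatment-emergent effects of SRT cannot be identified at all. The design does not support that. Randomisation gives a between-arm comparison at 6 and 12 weeks, and in every row above the difference keeps its sign. ISI, PHQ-9, GAD-7, FACT-F and a 7-day diary at T0 cover sleep, mood, anxiety and fatigue. They are, however, different instruments, with no rule linking them to inventory items.
- *Unseen instrument.* Its items and recall period are not given. If it asks about effects since starting treatment, a T0 reading in that form would mean little. This stands, so a T0 version must ask about current symptoms.
- *Table 2 is an overview.* It also omits EQ-5D-5L, which the text says is collected, so a blank cell alone is weak evidence. Here the text does not supply a baseline reading either.
- *Starting prevalence.* The Preparatory Research remark on SRT, "it may minimise these other prevalent cancer-related side effects as they emerge", concerns symptoms arising over the cancer course. It is not evidence of how common they are at T0.
- *Later cancer treatment.* Patients enter before chemotherapy or radiotherapy, so some later symptoms will be new for that reason. A T0 reading cannot remove them; only the SHE arm can.
- *Yield.* At b = 0.5, the comparison among symptom-free patients is about 2 of 10 against 0.5 of 10. The gain is in classifying individual patients, with little added between-arm precision.

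**Conclusion.** The point holds in a limited form. No pre-treatment inventory is scheduled, so onset or worsening on that instrument cannot be established for an individual patient, and relatedness grading lacks a same-instrument reference. Group-level comparison with SHE at 6 and 12 weeks remains possible but imprecise, at roughly ±27 to ±31 points with 20 per arm under the assumed rates.

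The consequence is modest. Safety is not a Table 1 success criterion, and the stopping rule (Criteria for Intervention Discontinuation) uses study-related serious events. Tolerability is also informed by attendance, attrition, satisfaction and exit interviews.

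The 38% to 88% range is illustrative only. It assumes the starting prevalence, full persistence of baseline symptoms and the rate of new symptoms, and the protocol supplies none of these. This is a cheap improvement, not a defect that undermines the pilot.

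**What to change.** Add a side-effects inventory row to Table 2 with a mark at Baseline (T0) in both arms. T0 falls after randomisation, so state that the form is completed before any SRT or SHE contact and is worded for current symptoms.

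Add one sentence to section 12.2: inventory symptoms that are new or worse than at T0 will be reported by arm, alongside the raw counts.

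The cost is one short form in an existing baseline battery, which is a few minutes of patient time, and one sentence of text. It will not separate SRT effects from those of later cancer treatment and will not make relatedness grading blind. The by-arm comparison remains necessary.

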# Interventions

- 1. Sleep Restriction Therapy (SRT)

SRT is a manualised, adaptive, behavioural insomnia intervention that is a key active ingredient within multi-component CBT-I. Our SRT protocol ([18](#_ENREF_18)) involves standardising and (where required) limiting a patient’s time in bed with the aim of increasing homeostatic sleep pressure, over-riding cognitive and physiological arousal, and strengthening circadian control of sleep ([12](#_ENREF_12)). Those randomised to the SRT arm will receive two online sessions supported by two telephone calls over a 4-week intervention phase. Face to face SRT sessions will be available to those who are unable to access online sessions. SRT will be delivered by a nurse therapist, trained by suitably experienced members of our team, during a half-day workshop. Based on patient baseline sleep diary data, the trained nurse therapist will work collaboratively with the patient to encourage good sleep health principles such as not extending time in bed during this stressful period, avoiding napping, and keeping regular bed/rise times etc. For those patients who require it (i.e., those who are already extending time in bed), the nurse therapist will work with the patient to develop a tailored sleep/wale schedule by restricting and adjusting time in bed accordingly.

• Session 1 (30 minutes) – The first session will be an online (Zoom) session. The nurse therapist will introduce the rationale for SRT, review baseline sleep diaries, focus on core SRT principles (not extending time in bed, avoiding napping, keeping regular bed/rise times) and prescribing new bed and rise-times (where required). Advice on the management of daytime sleepiness and discussion of barriers/facilitators to implementation will also be offered. Patients will also be given a booklet supporting home implementation of SRT and SHE guidance [19].

• Session 2 (15 minutes) – The nurse therapist will telephone the patient to check progress, provide an opportunity for questions, and advise on titration of the patient’s sleep schedule for the following week based on a structured algorithm [18].

• Session 3 (20 minutes) - The third session will follow the same structure as session two but will be an online session. The nurse therapist will review patient progress, explore (and attempt to overcome) barriers to implementation, and further titrate the sleep schedule (where required).

• Session 4 (10 minutes) – The nurse therapist will telephone the patient to check progress, provide an opportunity for questions, and advise on further titration of the patient’s sleep schedule if required. Suggestions for ongoing implementation and the management of residual or recurrent insomnia symptoms will also be provided during this final session.

- 1. Sleep Hygiene Education (SHE)

SHE will be delivered via a booklet that provides information about lifestyle changes (e.g., reducing exercise in the evening, light snack before bedtime, reducing caffeine) and changes to the bedroom environment (e.g., dark room, comfortable mattress, optimal room temperature). Patients in the SHE condition will be instructed to implement the SHE advice over a 4-week period. One week after randomisation to SHE, the RA will telephone patients to check they understand the SHE advice and answer any questions they may have. However, the SRT nurse therapist will have no input into delivery of SHE and will not review patients randomised to this condition. SHE has successfully been used as a control condition in other trials evaluating SRT and does not have any therapeutic benefit for individuals with insomnia but is often part of usual care, so is a credible alternative to SRT.

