The second stage of screening involves the completion of a semi-structured interview (on Qualtircs or administered by the researcher over Zoom/Teams or telephone) to establish full study eligibility. This includes assessment of current sleep status (based on diagnostic criteria for acute insomnia outlined in 6.1 above), current psychiatric symptoms and review of other relevant medical information (diagnosis of other sleep disorders, other medical and psychiatric disorders). This is to confirm the diagnosis of acute insomnia and establish that there are no medical or psychiatric conditions that might preclude someone from taking part in the study. During screening, we will also give each participant the opportunity to sign a health release form. This will give us permission to contact their health care provider of choice (e.g., their GP) with information that has been uncovered as part of their participation in this study (and only this information e.g., uncovering potential Major Depressive Disorder), that might warrant further follow-up but that cannot be provided as part of this trial. This will be an opt-in opportunity, and not signing the health release form will not have any impact on their participation in the study. In cases where the participant discloses suicidal ideation or physical/sexual abuse to them or others, the respective authorities will be contacted by the CI even if consent for this action is not provided by the participant. This is made clear to the participant in the participant information sheet and also verbally prior to screening. Once eligibility is ascertained, patients will be randomly assigned to SRT or the SHE control group.

- 1. Randomisation

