We aim to randomise 40 patients (n=20 in each trial arm), and conservatively estimate that we will recruit 5 patients per month across both sites in a 10-month recruitment window (assuming a dropout rate of 20%). This represents <10% of the total number of patients seen per month in these clinics. NHS Greater Glasgow and Clyde and NHS Grampian serve a combined population of around 1.7M. In the NHS GGC South Sector breast service, based at Gartnavel General Hospital, there are 550 new breast cancers each year, with over 60% of this population undergoing surgery as their primary treatment. In NHS Grampian, 545 new breast cancers (screening and symptomatic pathways) were diagnosed in 2021. About 84% of these newly diagnosed patients received surgery as their primary treatment. Of these, we conservatively estimate that 40% will meet criteria for acute insomnia (n=315). From these, we aim to randomise patients to take part in the study.

- 1. Study Assessment Points

After randomisation to SRT or SHE, patients will be sent an email with a link to complete a baseline (pre-intervention) assessment of sleep, fatigue, and mental health (questionnaires can be completed over the telephone or on paper should the participant prefer this). Patients will also be required to complete the consensus sleep diary and wear an actigraphy device for 7 days prior to commencement of SRT/SHE to record sleep and rest/activity rhythms. Within-treatment session outcomes for SRT will also be explored using sleep diaries and actigraphy. After completion of the baseline assessment, patients will either be referred to the nurse therapist for commencement of the SRT protocol or provided with the SHE resource. At 6 weeks, and 12 weeks post-randomisation, patients will be requested to complete the same battery of questionnaires as during the baseline assessment. Following completion of the final study assessment (12 weeks post-randomisation), those randomised to the SHE condition will be offered the opportunity to complete the SRT protocol without the requirement to complete any further assessments.

- 1. Primary and Secondary Outcomes

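### The one scheduled SHE support call is timed from randomisation, so it falls on the day the SHE booklet can first be provided, or before it

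*Protocol*

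**What the plan says.** Four statements in the protocol fix the order of events for a control patient.

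- Procedures, Patient Screening and Recruitment, puts randomisation directly after eligibility screening: "Once eligibility is ascertained, patients will be randomly assigned to SRT or the SHE control group".
- Procedures, Study Assessment Points, starts the baseline after that: "After randomisation to SRT or SHE, patients will be sent an email with a link to complete a baseline (pre-intervention) assessment". Patients also keep the sleep diary and must "wear an actigraphy device for 7 days prior to commencement of SRT/SHE to record sleep and rest/activity rhythms".
- The same section then releases the interventions, which for a control patient means the SHE resource: "After completion of the baseline assessment, patients will either be referred to the nurse therapist for commencement of the SRT protocol or provided with the" (the sentence closes by naming that resource). The SHE section identifies it: "SHE will be delivered via a booklet that provides information about lifestyle changes".
- Interventions, Sleep Hygiene Education, times the support call: "One week after randomisation to SHE, the RA will telephone patients to check they understand the SHE advice". The call is also for answering questions.

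Table 2 agrees with this order. It shows 7 days of diary and 7 days of actigraphy under Baseline (T0), and nothing for either under Screening. The SHE section gives patients 4 weeks to act on the advice. It describes no other SHE support contact and rules out any review by the SRT nurse therapist.

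**The concern.** The call is timed from randomisation, whereas the booklet is timed from the end of a baseline that itself begins after randomisation. A call meant to check that advice has been understood should follow receipt of the advice by enough time for it to be read. As written, it does not.

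Two things are at stake. First, SHE consists of a booklet and this one scheduled call. If the call comes too early, the control condition loses the only comprehension check described for it. Second, the baseline is meant to be free of intervention. If the research assistant explained the advice during the call, that could happen while baseline diary and actigraphy data were still being collected. Only the SHE arm would be exposed in this way, because SRT patients receive SHE guidance at Session 1, where their baseline diaries are reviewed.

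The quantitative fidelity criteria in Table 1 would not detect the problem. They cover SRT content, SRT attendance and SHE patients receiving SRT, but not delivery of SHE. The pilot is meant to inform the design of a full-scale trial, so an uncorrected timing rule could be carried forward.

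**Working it through.** This is a day count.

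**Inputs from the protocol**
- Randomisation: day 0.
- Call: one week after randomisation, day 7 (Sleep Hygiene Education).
- Baseline diary and actigraphy: 7 days, after randomisation and before SHE starts (Study Assessment Points; Table 2).
- Booklet: after the baseline is complete (Study Assessment Points).

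**Input not in the protocol**
- L, the number of days from randomisation to the start of diary and actigraphy. It is varied here from 0 to 14 as an assumption.

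**Formulae**
- Earliest booklet day = L + 7.
- Call day minus earliest booklet day = 7 − (L + 7) = −L.

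| Assumed L (days) | Earliest booklet day | Call day | Call minus booklet (days) |
|---|---|---|---|
| 0 | 7 | 7 | 0 |
| 1 | 8 | 7 | −1 |
| 3 | 10 | 7 | −3 |
| 7 | 14 | 7 | −7 |
| 14 | 21 | 7 | −14 |

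Since L cannot be negative, the call never falls after the earliest booklet day. For L from 1 to 7 it falls inside the baseline recording week. For L above 7 it falls before recording has begun. Any delay between the end of baseline and provision of the booklet widens the gap further.

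**Can another reading remove the conflict?** It would have to place the 7-day recording before randomisation. The recruitment text, Study Assessment Points and Table 2 all point the other way.

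**What is not touched.** The sample size in Data Analysis rests on an ISI difference of 4.2 and a standard deviation of 4.5. A two-sided 5% t-test with 80% power needs 19.03 per arm, rounded up to the stated 20, and 20 / (1 − 0.2) = 25 per arm to recruit. The timing of the call does not enter this. The planned 6-week ISI comparison is a t-test or Mann-Whitney test and, as described, uses no baseline data.

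**The case against.** The strongest reply is that this is loose wording for one week after SHE begins, and that sensible staff would delay the call until the booklet had been provided. That may well be the intention. But the text says randomisation, no other section corrects it, and staff who follow the SHE section as written will call on day 7.

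Four further points limit the finding, and they stand.

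- Only the same-day result follows from the documents alone. How far the call precedes the booklet depends on a start delay the protocol does not give. A reader might infer that nearly every control patient would be called several days early; the documents do not support this, because they do not say when the actigraph is handed over or the diary begun.
- A reader might infer that the SHE arm's baseline will be contaminated. That is only a possibility. It needs a late start to recording and a research assistant who discusses advice the patient does not yet hold.
- A reader might infer that the SRT versus SHE comparison is undermined. The protocol regards SHE as having no therapeutic effect on insomnia, no Table 1 criterion depends on the call, and the 6-week ISI test uses no baseline data. A material effect on outcomes cannot be claimed.
- It would be too strong to call this the control arm's only human contact, or to say that control procedures go unexamined. Questionnaires may be completed by telephone, patients are encouraged to contact the team, and the qualitative process evaluation interviews 5 control patients. The supportable statement is that this is the only scheduled SHE support call described.

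**Conclusion.** The conflict is real and lies in the protocol's own text. The call falls on the earliest day the booklet can be provided if recording starts on the day of randomisation, and L days before that if recording starts L days late. This result assumes only that the order in Study Assessment Points is followed and that one week means 7 days. The size of L is unknown.

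Followed as written, the call cannot serve its stated purpose, and it leaves open the possibility of intervention contact during the baseline week in one arm. The consequence is confined to delivery of the control condition and, possibly, to its baseline diary and actigraphy data. The sample size and the 6-week ISI test stand.

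**What to change.** Reconcile Study Assessment Points with the Sleep Hygiene Education section so that the timing of the call is consistent with when the booklet is provided and with completion of the baseline week. The choice of anchor and interval belongs to the study team. Record, for each SHE patient, the date the booklet was provided and the date of the call, so that the pilot can show how the control condition was delivered.

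The cost is a short wording change and two logged dates, with the same single call. The schedule has room for it. With L = 0, the 4-week SHE period runs from day 7 to day 35 (7 + 28), and the 6-week assessment is due on day 42.
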